### **3. Project Summary**

#### **3.1 Brief Summary**

##### **3.1.1 Introduction, background, objectives**

Thailand targets high risk groups for annual immunization with trivalent inactivated influenza vaccine (IIV3), including persons aged 65 years and older. However, there are few data from Thailand on the effectiveness of IIV3 in preventing influenza-associated illness and hospitalizations, and even fewer data on the cost-effectiveness of vaccination. This is a prospective population-based cohort study of persons aged 65 years and older that will compare the incidence of influenza-associated acute respiratory infection (ARI) and influenza-associated severe acute respiratory infection (SARI) between individuals who do and do not receive the influenza vaccine to measure the reduction in disease associated with IIV3. We will enroll and collect nasal self-swabs from randomly selected elderly each time they experience an ARI in two districts of Nakhon Phanom and test them for influenza. If they are hospitalized with SARI, a nurse will take a nasopharyngeal swab to test for influenza. Data on factors associated with vaccination will be measured and propensity for vaccination will be modeled in order to account for potential biases in the analysis. We will follow these elderly participants for two years and compare the number of influenza-associated ARI and SARI events between elderly that were vaccinated and elderly that were not vaccinated to calculate how effective IIV3 was in preventing influenza. This study will also evaluate the cost-effectiveness of IIV3 vaccine. Additionally, this study will measure the effect of having ARIs/SARIs on functional status, the VE of IIV3 in preventing influenza associated exacerbations among participants with chronic obstructive pulmonary disease(COPD), the duration of adequate IIV3 antibody levels in blood, and the incidence of respiratory syncytial virus (RSV) among the elderly.

### **3.1.2 Location of the study**

The study will be conducted in Nakhon Phanom (NP) Province. This province was selected because of a history of collaborating with TUC on research and surveillance and an interest from the Provincial Health Office to increase influenza vaccination coverage among the elderly. Nakhon Phanom has 12 districts, 10 of which are suitable for studies (two districts had a high probability of becoming flooded during the rainy season making movements difficult). In 2014, 4 of the 10 districts were systematically selected to be involved in the Influenza Vaccination Campaign run by the MOPH where high-risk community members were encouraged to become vaccinated; a similar campaign is being planned for 2015. Our study will sample from two of the four districts involved in the campaign to ensure that there are enough elderly members who became vaccinated in these districts to measure vaccine effectiveness. The two districts are That Phanom and Plapak which were chosen due to feasibility of location and consent of district health directors.

### **3.1.3 Duration of the study**

We will begin recruiting and training healthcare volunteers, nurse practitioners and nurses on data collection and laboratory technique in February of 2015 through April 2015. Participants will be enrolled in the study by June 2015 and followed for two years. Additionally, approximately six more months will be needed after the study to analyze data, which will begin in June 2017. The entire study will take approximately 2 years and 10 months.

### **3.1.4 Study design, methodology, study plan**

Persons aged 65 years and older will be recruited in the two selected districts of Nakhon Phanom Province and followed weekly for one year to identify any new episodes of ARI or SARI. Baseline information will be collected from all participants, including functional status and frailty indicators, chronic diseases, smoking history, and variables related to socioeconomic status. Participants will be asked how far the closest health center is from them and household latitude and longitude will be collected in order to calculate distances to medical facilities. ARI will be defined as a new onset of cough or worsening of chronic cough, with or without fever.

SARI will be defined as new onset of cough, worsening of chronic cough or difficulty breathing with a fever  $\geq 38^{\circ}$  Celsius that requires hospitalization. Nasal and nasopharyngeal samples taken from persons with ARI or SARI will be tested using real-time reverse-transcription polymerase chain reaction (rRT-PCR) for influenza and respiratory syncytial viruses. The incidence of laboratory-confirmed, influenza-associated ARI and SARI will be compared between vaccinated and unvaccinated cohort participants, controlling for baseline functional status and underlying medical conditions that might confound the primary association. Data on costs of visits for ARI and SARI for pneumonia or acute respiratory illness will be collected, along with information on the costs of the vaccination campaign, to determine the cost per influenza episode averted and the value for money of the immunization campaign. Results will assist the Thai Ministry of Public Health to make informed decisions related to improving vaccination coverage among the elderly in Thailand.

In addition to vaccine effectiveness and cost effectiveness data, this study will also take the opportunity to measure the effect of ARI and SARI on functional status among the elderly, measure the incidence of influenza-associated COPD exacerbations among those with ARI or SARI, evaluate humoral immune response of IIV3 through measurement of hemagglutination inhibition assay (HAI), and measure the incidence of respiratory syncytial virus (RSV) among the elderly with ARI or SARI.

Vaccination: Cohort participants, along with all persons aged 65 years and older in the districts identified by the MOPH for increased IIV3 coverage, will be eligible for influenza vaccination through routine vaccine delivery strategies used by the MOPH. No vaccine will be provided as part of this protocol. The study will be enrolling participants from two districts in Nakhon Phanom, That Phanom and Plapak. According to the Nakhon Phanom Provincial Health Office, the vaccination rate in 2014 was calculated to be 52% and 28% in That Phanom and Plapak, respectively. This VE study will follow a pilot program of the MOPH to increase vaccination among the elderly through a concentrated and focused vaccine campaign in the elderly. This year, due to planned vaccination campaigns, we expect the vaccination rate to be around 50% in both districts. A companion study to this protocol, already underway, will evaluate the coverage achieved by the pilot campaign as well as measure factors associated with receipt of the vaccine in this age group.

Influenza surveillance: Contact information, including phone numbers, will be recorded for all cohort participants. Health volunteers will contact all participants weekly for one year to identify any individual with new onset of cough or worsening of chronic cough, with or without fever (ARI) and any individuals with cough and fever  $\geq 38^{\circ}\text{C}$  requiring hospitalization (SARI). There are a number of diagnostic specimens that have been used to identify the viral etiology of ARI/SARI, including nasal, nasopharyngeal (NP) and oropharyngeal (OP) swabs. The most acceptable of these to patients is the nasal swab, as it is less invasive (1). Individuals with new onset of cough or worsening of chronic cough will be asked to take a nasal self-swab and properly store the sample in a separate tube. If the participant is too ill to be able to take a self-nasal swab, they will ask their assigned health volunteer to schedule a time to assist them in taking the swab. They will also be encouraged to seek medical attention at the sub-district health center, district hospital or provincial hospital where trained study staff is located if they are feeling very ill. The study will facilitate transport to the local health center for any severely ill participants who are unable to transport themselves. Trained research nurses in the hospital will take nasopharyngeal swabs for influenza diagnosis from admitted participants, and routine clinical information will be recorded. Nasopharyngeal swabs have been shown to be comparable to oropharyngeal swabs for detecting Influenza A and equal or superior to oropharyngeal swabs for detecting Influenza B (2, 3).

Laboratory testing of nasal and nasopharyngeal swabs: Nasal self-swabs from participants will be stored in transport media (TM) and immediately transported with ice packs to the sub-district health center by a health volunteer and placed into a refrigerator monitored to be between 2 to  $8^{\circ}\text{C}$  for a maximum of 24 hours. From there, the specimens will be transported to the district hospital in ice packs where they will be stored in liquid nitrogen tanks within 24 hours. Nasopharyngeal swabs taken by nurses will also be stored at the local health center in a regulated refrigerator for a maximum of 24 hours and transported to the district hospital with ice packs to be stored in liquid nitrogen tanks. All respiratory specimens will then be transported to the MOPH National Institute of Health (NIH) laboratory in Nonthaburi in liquid nitrogen tanks where they will be tested using rRT-PCR for influenza and RSV using protocols developed by CDC (4). If specimens will not be tested immediately upon arrival at the laboratory, they will be stored below  $-70^{\circ}\text{C}$  until tested.

Laboratory testing of blood samples: In order to measure hemagglutination inhibition assay (HAI) antibody titers to check for duration of seroconversion in elderly from IIV3, blood samples will be requested from elderly arriving to the district hospitals vaccination clinics in That Phanom and Plapak for vaccination. The first sample will be taken just before vaccine is administered on day 0 (as a baseline measurement) and on day 28 (after 1 month), day 180 (after 6 months) and day 360 (after 1 year). One additional blood draw will be requested after 28 days of vaccination in the second year to compare the effect of prior vaccination on level of immunological response. Participants will be expected to go to their district hospital to have their scheduled blood draw. Blood will be drawn at the participant's home if they are unable to travel to their district hospital by a research nurse. Blood samples will be collected and immediately sent to the district hospital lab to separate the serum from the blood (if blood is collected at a participant's home, it can be transported back to the district hospital with the nurse at room temperature). The serum will be stored in a refrigerator between 4-8°C for no longer than seven days and transported to NIH on a weekly basis. During transport to NIH, serum samples will be stored with ice packs for less than 24 hours. Upon reaching NIH, the samples will be measured using a standard HAI (5). Seroconversion will be measured as the percent of participants who have one of the following: a baseline HAI titer of  $<10$  and a post vaccination titer of  $\geq 40$ ; or a baseline HAI titer of  $\geq 10$  and a  $\geq 4$  fold increase post vaccination (6). Using HAI response as a correlate of protection, we will also be able to estimate the duration of protection and correlate immunologic outcomes with influenza-associated ARI and SARI among the elderly.

Cost data: Records from the Provincial Medical Office and the National Health Services Office will be used to determine the cost of the vaccination campaign, which will be converted into a per capita cost per vaccinee. Data from the Provincial Medical Office will also be collected on average cost of outpatient visits for acute respiratory infection and inpatient admissions for pneumonia. We will also account for indirect costs of missing work days for elderly and their caregivers, and transportation cost. This information will be used to determine the cost-effectiveness of IIV3 among the elderly.

Functional Status:

Participants will be questioned at enrollment about their functional status along with other baseline medical conditions such as co-morbidities using a standardized questionnaire. Functional status is the individual's ability to perform normal activities of daily living. We will use the index from the Vulnerable Elders Survey (7) along with individual elements from other indices and test their association with ARI to determine if experiencing ARIs or SARIs impacts functional status. Cognitive function will be self-assessed as other measures require trained medical personnel to implement. Vulnerable Elders Survey (VES-13) is a function-based questionnaire that was developed to screen elderly 65 years of age or greater in the community to determine their risk for health deterioration (7, 8). The questionnaire asks elderly to self-report their age, health, limitations in physical function and functional disabilities, and takes an average of less than five minutes to complete(7, 8). This tool can be administered over the phone or in person. Each response to each question on the form has a point value attached ranging from 0 to 3 points, and it is scored by adding up points based on the responses received, up to 10.(8) Scores  $\geq 3$  indicate frailty associated with increased mortality. The test has been shown to be reliable (7, 9, 10). The same functional status measurements were used in a companion study which assessed whether functional status correlated with obtaining flu vaccine and has already been translated into Thai. Using the same functional status measurement tool in this study will allow us to compare outcomes between both studies and build upon prior conclusions. Participants will be asked to re-take the functional status VES-13 questionnaire every six months during the study period to measure changes in functional status over time.

In order to measure the impact of the first episode of ARI or SARI on functional status, we will conduct a nested case-control study of participants recovering from an ARI or SARI. Participants who experience their first ARI or SARI after enrollment will be matched with cohort participants who have not yet experienced an ARI or SARI based on age ( $\pm 5$  years), sex, influenza vaccination and most recent functional status measurement. Interviews will be conducted three to four weeks after the onset of ARI or SARI in the case and both cases and controls will be compared with respect to changes in functional status measurement (VES-13 score  $\geq 3$ ).

Elderly with COPD: In the standardized baseline questionnaire assessing functional status and medical conditions, participants will be asked whether they have been diagnosed with COPD. If they do, at the end of two years, the number of outpatient visits and inpatient admissions for exacerbations of COPD will be determined (by directly observing their medical records). A COPD exacerbation is defined as “a sustained worsening of the patient's condition, from the stable state and beyond normal day-to-day variations that is acute in onset and may warrant additional treatment in a patient with underlying COPD” (11). We will use the collected nasal self-swabs or healthcare worker collected nasopharyngeal swab taken when the participant was experiencing an ARI or SARI to confirm whether the COPD exacerbations the participant experienced were influenza-associated. At the end of the study, the incidence of all-cause COPD exacerbations and laboratory confirmed influenza-associated COPD exacerbations among the elderly with COPD who fit the ARI or SARI case definitions will be calculated. The incidence among those who were vaccinated will be compared to those who were not vaccinated.

Pilot studies: Vaccination coverage of persons aged 65 years and older in Nakhon Phanom is low, and targeted towards the elderly who also have underlying chronic conditions. The Provincial Medical Office undertook a pilot study in four districts from June-November 2014 to evaluate strategies to increase the vaccination rate and identify factors, such as functional status and chronic medical conditions that are significantly associated with vaccination. The information gained from this study will allow increased precision in sample size estimates and improved measurement of potential confounders. Another pilot study was conducted from February to March 2015 that studied the acceptability, accuracy and validity of taking nasal self-swabs. Of the total 108 participants in the study, all 108 participants (100%) felt that taking the nasal swab by themselves was acceptable, Sixteen participants (15%) felt uncomfortable taking the swab by themselves; however, 107 participants (99%) felt that nasal self-swabbing was easy to perform. Out of the 109 nasal self-swab samples collected, 106 (97.2%) were able to detect RNaseP<37, an indicator that the samples were taken accurately. We are still in the process of analyzing the validity of the data collected.

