#### **7.1.5 Number of participants**

Sample size for cohort: The cohort sample size is calculated assuming a 50% vaccination rate, 80% power, a probability of committing a type I error of 5% and an incidence of influenza-associated ARI of 6% per year. With an expected VE of 40% based on our population's age and past studies (12, 16, 17), the required sample size is 2,724. Given a 15% loss to follow-up, a total of 3,133 persons should be enrolled, and assuming a 10% refusal rate, a total of 3,446, or, for simplicity, 3,500 individuals need to be selected

These sample sizes were calculated in OpenEpi.com(47) using the Fleiss Method with a correction factor as follows:

Fleiss Method:

$$n_1 = \frac{[Z_{\alpha}\sqrt{(r+1)\bar{p}\bar{q}} + Z_{1-\beta}\sqrt{rp_1q_1 + p_2q_2}]^2}{r(p_1 - q_1)^2}$$

$$n_2 = rn_1$$

where  $n_1$  is the number of cases and  $n_2$  is the number of controls,  $\bar{p}$  is the average exposure in the population,  $\bar{q}$  is  $1-\bar{p}$ ,  $p_1$  is the proportion of cases with the exposure,  $q_1$  is  $1-p_1$ ,  $p_2$  is the proportion of controls with exposure and  $q_2$  is  $1-p_2$ .

To account for the use of a normal distribution to approximate a binary function, a continuity correction is applied to  $n_1$  as follows to calculate the final sample size,  $n_{cc}$ :

$$n_{1cc} = \frac{n_1}{4} \left[ 1 + \sqrt{1 + \frac{2(r+1)}{n_1 r |p_2 - p_1|}} \right]^2$$

$$n_{2cc} = rn_{1cc}$$

where  $n_{1cc}$  and  $n_{2cc}$  are the corrected sample sizes of  $n_1$  and  $n_2$ , respectively.

Sample size for changes in functional status related to ARI or SARI: We will select matched pairs and compare functional status (measured on a 10 point scale by the VES-13) three-four weeks after the onset of an influenza-associated ARI or SARI to a control who has not had an ARI or SARI. As functional status is measured on continuous scale of 1-10, a matched dependent  $t$  test is used to compute sample sizes. We have used the PROC POWER procedure in SAS

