### **For primary objective 1.2 (Direct and Indirect costs)**

When a participant becomes ill due to an ARI or SARI, we will train health volunteers to ask them about their costs associated with the infection with an electronic questionnaire CRF 1 week after recovering from their illness. If the participant went to a public health center or hospital, staff authorized by the hospital director will check their medical records to determine the cost of the visit. If the participant went to a private clinic, the standardized questionnaire will ask about the amount of money they and their insurance spent in order to treat/get treated for their illness including all laboratory and examination tests, clinician fees, hospital fees, medication fees. The questionnaire will also ask all participants regarding cost of over-the-

counter medications including herbal or traditional medicine costs, transportation fees, and questions to determine how much income their household lost due to missed work days of the elderly participant and of caregivers who take care of the participant to calculate indirect cost.

Records from the Provincial Medical Office and the National Health Services Office will be used to determine the cost of the vaccination campaign, which will be converted into a per capita cost per vaccinee. Data from the Provincial Medical Office will also be collected on average cost of outpatient visits for acute respiratory infection and inpatient admissions for pneumonia.

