## **8.2 Compensation**

The money used to compensate participants is minimal and only available in order to defer the cost of time, transportation, and phone calls so that participating in the study will be neither a burden nor an incentive for making money. All participants will be compensated with a total of 1000 baht per year for their time and phone calls to health volunteers for a total of 2,000 baht for the entire study period. They will initially receive 300 baht upon enrolling in the study. They will receive another 300 baht after 6 months if they are still enrolled, and 400 baht after 12 months. If they stay enrolled for the second year, they will be reimbursed the same way as the first year. If participants need to go to the local health center for a clinical visit, they will be compensated 100 baht for transportation. Participants enrolled in the immunogenicity study will receive 300 baht with each blood draw, so they will get a total of 1,200 baht for the year 1 and additional 300 baht (total 1,200 baht) for year 2 of the immunogenicity study if they remain enrolled. As mentioned and outlined in section 7.8, all participants' personal information will remain confidential and secure.

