|    |                                                                                                                                                           |                                                                                         |                                     |
|----|-----------------------------------------------------------------------------------------------------------------------------------------------------------|-----------------------------------------------------------------------------------------|-------------------------------------|
| 23 | Other sources                                                                                                                                             | 1 Yes

2 No                                                                       | If No,
skip to
question
25 |
| 24 | Specify                                                                                                                                                   | _____                                                                                   |                                     |
| 25 | How much money did you spend on transportation fees to and from all visits to hospitals and clinics?                                                      | _____ Thai baht                                                                         |                                     |
| 26 | How much money did you spend on all medications not provided by the hospital or clinic (including herbals) and treatments (including traditional healers) | _____ Thai baht                                                                         |                                     |
| 27 | Which public health-centers/hospitals did you visit for your illness?                                                                                     | Please List:

1 _____

2 _____

3 _____

4 _____

5 _____ |                                     |
| 28 | Did you visit any private health centers during your illness?                                                                                             | 1 Yes

2 No

77 Do Not Know

99 Declined to answer                    |                                     |

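### The cost per influenza episode averted counts household travel and lost work for illness but not for vaccination, an additive understatement of about 42 baht for each baht omitted per vaccinee

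*Protocol*

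**What the plan says.** Primary objective 1.2 (Section 5) covers direct and indirect costs of influenza, the savings from vaccination and the campaign's value for money. Section 3.1.4 names the outcome as a cost per influenza episode averted.

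- **Vaccination side.** Section 3.1.4 (Cost data) states: "Records from the Provincial Medical Office and the National Health Services Office will be used to determine the cost of the vaccination campaign". The total becomes a cost per vaccinee. Section 7.5.1, under primary objective 1.2, repeats this and adds no other component.
- **Illness side.** Section 7.5.1 has health volunteers administer a cost questionnaire one week after recovery. It covers treatment, over-the-counter and herbal medicines, fares, and "questions to determine how much income their household lost due to missed work days of the elderly participant and of caregivers". Form 4g carries this out; its transport item reads "How much money did you spend on transportation fees to and from all visits to hospitals and clinics", and its work-loss item is tied to the illness.
- **Text that names no side.** Section 3.1.4 adds "We will also account for indirect costs of missing work days for elderly and their caregivers, and transportation cost". Section 7.9 takes direct and indirect costs from the vaccinated and unvaccinated groups.

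The enrollment form (4b), weekly form (4c), episode forms (4d, 4e) and immunogenicity form (4h) have no item on the fare, time or escort cost of a vaccination visit.

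**The concern.** The two sides of one ratio use different costing perspectives. Household fares and lost work raise the value of each prevented illness, while the same kinds of cost borne in order to be vaccinated are absent. Every vaccinee may bear the omitted cost, but the saving arises only in the few whose influenza is prevented, so a small amount per person is multiplied when expressed per episode averted. Taken alone, this omission can only make vaccination look better.

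The objective is primary and the result is meant to inform the Ministry's decisions on coverage. Section 4.2 itself cites an earlier study suggesting that vaccinating the elderly may not give sufficient value for money, so a one-directional costing gap deserves closing.

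**Working it through.** **Inputs (Section 7.1.5).** "an incidence of influenza-associated ARI of 6% per year"; "With an expected VE of 40% based on our population's age and past studies"; "assuming a 50% vaccination rate, 80% power"; type I error 5%. The cost c that a vaccinee and escort bear to obtain one dose is not in the documents; it is an assumption, shown as a range.

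**1. Which risk is the 6%?** The stated cohort size is 2,724. Take 6% as the unvaccinated risk, so the vaccinated risk is 0.06 x (1 - 0.40) = 0.036.

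- Fleiss, two-sided 5%, 80% power, 1:1: 1,245 per group.
- With continuity correction: (1,245/4) x [1 + sqrt(1 + 4/(1,245 x 0.024))]^2 = 1,327 per group, 2,654 in total.
- This is 2.6% below 2,724: close, not exact.
- If 6% were the overall cohort incidence, the risks would be 7.5% and 4.5% (0.06/0.8 = 0.075), giving 2,098. A one-sided test gives 2,124; no continuity correction gives 2,490.

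The unvaccinated-risk reading fits best and is used below.

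**2. Vaccinees per episode averted.** 1/(incidence x VE) = 1/(0.06 x 0.40) = 1/0.024 = 41.7.

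**3. Effect of an omitted cost.** Let V be the number vaccinated, P the programme cost per vaccinee, S the total illness savings and E the episodes averted.

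- As planned: (V x P - S)/E.
- With vaccinee-borne cost: (V x (P + c) - S)/E.
- Difference: (V/E) x c = 41.7 x c.

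The difference is the same whether or not savings are netted off.

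| assumed c (baht) | understatement per episode averted (baht) |
|---|---|
| 0 | 0 |
| 10 | 417 |
| 20 | 833 |
| 50 | 2,083 |
| 100 | 4,167 |
| 200 | 8,333 |

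**4. Sensitivity of the multiplier.** At 6% unvaccinated incidence: VE 50%, 1/0.030 = 33.3; VE 30%, 1/0.018 = 55.6. If 6% were overall incidence at VE 40%, 1/(0.075 x 0.40) = 33.3.

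**5. Why this is not a 42-fold error.** The ratio of corrected to planned gross cost is (P + c)/P; the 41.7 cancels. For illustration only, P = 200 and c = 50 (both assumptions) give 8,333 and 10,417 baht per episode, a ratio of 1.25. The protocol gives neither P nor a cost per episode, so the proportional error cannot be computed.

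**The case against.** The strongest reply is that c may be small. The Limitations section says vaccine is free, Section 7.6 describes mobile vaccination clinics in the community, and people already attending care may need no extra trip. This stands: the size in baht is unknown and could be near zero for some doses. But vaccination also takes place at district hospitals, so zero cannot be assumed for all.

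A second reply is that the general sentence in Section 3.1.4 on work days and transport names no side, and that Section 7.9 takes costs from both groups. As wording this is fair, but it does not close the gap: Section 7.5.1 and form 4g apply those items to illness only, and no instrument supplies vaccinee-borne costs. An analysis plan could state a perspective or impute travel from the coordinates and distances collected. The protocol, however, fixes the cost sources on both sides and names distance only as a model covariate (Section 7.9).

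Three stronger readings are tempting and are not supported:

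- A 42-fold error. The multiplier applies to c alone.
- 100 baht as the protocol's vaccination fare. Section 8.2 says of participants going to the local health center for a clinical visit that "they will be compensated 100 baht for transportation". That is a study reimbursement, not a measured fare, and it does not concern vaccination.
- A final figure that must favour vaccination overall. Form 4g asks how many work days the participant missed but not the participant's own earnings, which may understate illness savings. The net direction is not established.

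**Conclusion.** The mismatch is in the protocol and should be corrected: illness costs follow a household view, vaccination costs a provider view, and no printed form collects the missing component. Its effect is an understatement of the cost per episode averted by about 42 x c baht at 6% incidence and 40% VE (33 to 56 times c for VE from 50% down to 30%). Over an assumed c of 10 to 200 baht this is about 417 to 8,333 baht, falling to nothing as c approaches zero. The multiplier rests on planning values and will move with observed incidence and VE. The conclusion is a one-directional omission of unknown size in a primary objective.

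**What to change.** Amend Section 3.1.4 (Cost data), the objective 1.2 text in Section 7.5.1, and Section 7.9 to state the costing perspective and report two cases, each consistent on both sides:

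- **(a) Provider case:** no household fares or lost work on either side.
- **(b) Societal case:** keep the indirect costs that objective 1.2 requires, and add vaccinee and escort travel and time to the cost per vaccinee.

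For (b), there are two sources. One is imputation from the household coordinates and health-center distance already collected, with a stated unit cost and a range that includes zero for mobile-clinic doses. The other is a short item added to a form used across the whole cohort. Form 4c could carry it but has no vaccination question at present, so one would have to be added. Form 4h is not a substitute: it reaches only the 384-person immunogenicity sub-study, whose members the Limitations section expects to be sicker than the general elderly population. The 100 baht reimbursement should not be entered as a measured fare.

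The cost is a little extra analysis, or one short item, and possibly a less favourable cost-effectiveness figure.
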